## Abstract

**Background:**

Back pain, one of the most prevalent conditions afflicting American adults, is the leading reason for using complementary and alternative medicine (CAM) therapies. Yoga is an increasingly popular "mind-body" CAM therapy often used for relieving back pain and several small studies have found yoga effective for this condition. This study will assess whether yoga is effective for treating chronic low back pain compared with self care and exercise and will explore the mechanisms responsible for any observed benefits.

**Methods/Design:**

A total of 210 participants with low back pain lasting at least 3 months will be recruited from primary care clinics of a large healthcare system based in Seattle. They will be randomized in a 2:2:1 ratio to receive 12 weekly yoga classes, 12 weekly conventional therapeutic exercise classes of comparable physical exertion, or a self-care book. Interviewers masked to participants' treatment group will assess outcomes at baseline and 6, 12 and 26 weeks after randomization. Primary outcomes will be back-related dysfunction and symptom bothersomeness. In addition, data will be collected on physical measurements (e.g., flexion) at baseline and 12 weeks and saliva samples will be obtained at baseline, 6 and 12 weeks. Information will be collected on specific physical, psychological, and physiological factors to allow exploration of possible mechanisms of action through which yoga could relieve back pain and dysfunction. The effectiveness of yoga will be assessed using analysis of covariance (using general estimating equations - GEE) within an intention-to-treat context. If yoga is found effective, further analyses will explore whether yoga's benefits are attributable to physical, psychological and/or physiological factors.

**Conclusions:**

This study will provide the clearest evidence to date about the value of yoga as a therapeutic option for treating chronic back pain, and if the results are positive, will help focus future, more in-depth, research on the most promising potential mechanisms of action identified by this study.

**Trial registration:**

This trial is registered in ClinicalTrials.gov, with the ID number of *NCT00447668*.

## Background

Back pain is a common and costly health problem, with more than 50% of adults bothered by it each year [1] and 70% to 80% of adults afflicted by it at some time in their lives [2]. It is the most costly ailment of working age adults, with an estimated $33 billion spent annually on medical costs [3] and an estimated loss of $19.8 billion due to loss of worker productivity [4].

Although there are a wide variety of treatments for back pain, including medications, exercise, education, self-care, injections, life-style aids, manual therapies, complementary and alternative medicine (CAM) therapies, minimally invasive treatments and surgery, there is surprisingly little consistent evidence to support most of these treatments [5], due to unavailable, insufficient or conflicting evidence. However, low back pain patients are relatively dissatisfied with their medical care [6], especially in comparison to care provided by non-physician's [7-10]. Eisenberg [11] found that most people with back problems considered CAM care to be superior to conventional medical care for back pain.

### Yoga as a treatment for back pain

One of the most popular CAM therapies for back pain is yoga [12,13], (a mind-body intervention whose practice often includes physical exercise coupled with a focus on breathing to increase awareness. In 1997, an estimated 1.3 million Americans used yoga for relief of back pain, attending 9.1 million classes. According to national surveys, yoga practice has increased since then, with over 10 million Americans practicing yoga for health reasons in 2002 [14] and over 13 million in 2007 [15], although no published information indicates how many American practice yoga to relieve back pain.

In a review of 17 non-pharmacological therapies for low back pain that forms the basis of clinical practice guidelines issued by the American Pain Society and the American College of Physicians, Chou [16] found "fair evidence" (i.e., the strength of the evidence was limited by the number, quality, size, or consistency of the included evidence) that yoga is an effective treatment for this condition.

We found no systematic reviews of yoga for low back pain. However, six trials on this topic have been published [17-22], four of which suffered from very small samples, lack of a control group, high loss to follow-up, and/or only short-term follow-up (one week). One of the larger studies, with 28% drop-out from the yoga group, found yoga superior to standard care plus education at the end of 24 weeks of biweekly classes [22]. The most scientifically rigorous trial, with 101 participants, found yoga superior to the exercise and the self-care comparison groups by the end of the 12 week intervention period [19].

### Putative mechanisms for yoga's benefit on back pain

While the mechanisms of action responsible for yoga's potential positive effects on back pain patients are unclear, there are a number of plausible mechanisms, including physical movement, relief of physical and mental stress, and enhanced body awareness to reduce maladaptive movements and posture [19]. Figure 1 depicts a heuristic model, derived from the literature and comments from yoga teachers and participants in an earlier study of yoga [19]. The model includes several pathways by which yoga might improve back-related dysfunction or pain. The model hypothesizes that yoga may decrease the pain and/or dysfunction of persons with chronic back pain through positive effects on one or more of three major pathways: physical functioning of the back, cognitive appraisal about back pain, and general affect and stress. We further hypothesize that any positive effects of yoga on affect and stress will be associated with improvements in neuroendocrine stress mediators. These hypothetical pathways provide a framework for testing some of the most important potential mechanisms of action for yoga and for identifying which ones are most promising for future research. The hypothesized pathways by which yoga may lead to improved outcomes for persons with back pain are indicated in Figure 1 by solid arrows. The broken arrows represent some of the most important hypothesized secondary relationships. We consider model testing in this trial as exploratory with the primary goal of laying the groundwork for future studies that will more definitively elucidate yoga's mechanisms of action in the relief of back pain.

**Figure 1 F1:**
[figure not shown]
**Model describing possible mechanisms underlying the effectiveness of yoga for chronic low back pain**.

### Specific aims

To conduct a randomized clinical trial that will evaluate whether:

1. Yoga is an effective treatment for chronic back pain (i.e., superior to self care) in terms of improved function and reduced pain.

2. Yoga is superior to a conventional treatment ("therapeutic exercise"), which consists of similar amounts of stretching and gentle strengthening exercises, in terms of improved function and reduced pain.

If the benefits of yoga are confirmed, analyses will be performed to:

3. Identify specific psychological, physiological or physical factors that help explain (i.e., act as mediators) the beneficial effects of yoga.

The study hypotheses directly reflect the specific efficacy aims.

***Hypothesis 1: ***Yoga is more effective than self care. A finding that yoga is more effective than self care would confirm the results of smaller studies that yoga is a useful treatment for chronic back pain.

***Hypothesis 2: ***Yoga is more effective than conventional therapeutic exercise consisting of stretching and gentle strengthening exercises. A finding that yoga is more effective than stretching/strengthening exercises would suggest that yoga has additional benefits for back pain patients beyond physical movement per se.

If yoga is found superior to the self care and/or exercise control, we will investigate the mechanistic aim, which is more exploratory. The hypotheses are:

***Hypothesis 3: ***One or more of the "cognitive appraisal" variables (improvements in body awareness and/or self- efficacy, decreased fear avoidance) act as mediators of yoga's beneficial effects.

***Hypothesis 4: ***One or more of the "affect and stress" variables (improvements in psychological distress, perceived stress, and positive affect) act as mediators of yoga's beneficial effects.

***Hypothesis 5: ***One or more of the "physical function" variables act as mediators of yoga's beneficial effects.

***Hypothesis 6***: One or both of the "neuroendocrine function" variables (cortisol and DHEA) act as mediators of yoga's beneficial effects.

Identifying specific variables that act as mediators would help us understand better how yoga might actually exert its benefits.

## Methods/Design

### Overview

Approximately 210 persons with chronic low back pain will be randomized in a 2:2:1 ratio to receive 12 weekly 75-minute yoga classes, 12 weekly 75-minute conventional therapeutic exercise classes, or a self-care book (Figure 2). Back-related dysfunction and symptom bothersomeness, the primary outcomes, as well as potential psychological (cognitive and affective) mediators will be assessed at 6, 12, and 26 weeks post-randomization by telephone interviewers unaware of treatment assignment. Physical function (a physical mediator) will be assessed at 12 weeks post-randomization by a nurse practitioner unaware of treatment assignment. Finally, saliva samples will be collected at 6 and 12 weeks post-randomization to assay for cortisol and DHEA (dehydropiandrosterone), biomarkers that may be influenced by yoga practice. Statistical analyses will assess whether yoga is superior to exercise and/or a self-care book. If there is a benefit for yoga, additional analyses will explore potential mediating variables.

**Figure 2 F2:**
[figure not shown]
**Participant-focused flow chart**.

Bias will be minimized by a rigorous randomization procedure, by describing the study as one of three different "lifestyle approaches" to treating back pain, and by masking both interviewers and the nurse practitioner making physical measurements to the participant's treatment group.

### Study population

Participants will be recruited from Group Health Cooperative, a group-model, not-for-profit health care organization that serves over 400,000 members through its own primary care facilities in Western Washington. Group Health members with chronic low back pain of non-specific origin (as opposed to infectious, neoplastic, or inflammatory causes) will be eligible to participate.

### Inclusion and exclusion criteria

Health plan members from 20 through 64 years of age with ICD-9 diagnoses indicative of non-specific low back pain and whose pain has persisted at least three months will be eligible for the study if they rate their pain at least 3 on a 0 to 10 back pain bothersomeness scale and give informed consent. Non-specific low back pain was chosen as the condition for study because it is a common and expensive problem and a leading reason for the therapeutic use of yoga. Inclusion and exclusion criteria were developed to maximize the enrollment of appropriate patients while screening out patients who: have low back pain of a specific (e.g., spinal stenosis) or complicated (e.g., due to a medical condition) nature, for whom yoga or exercise is contraindicated (e.g., severe disk disease), or whose medical conditions might make it difficult or impossible to participate in the classes (e.g., gross obesity). These criteria are intended to exclude patients with medical conditions that might contribute to an increased risk of an adverse event, preclude fully informed consent (e.g., dementia), or lead to misinterpretation of the data (e.g., multiple sclerosis or diabetes with neurological symptoms that might interfere with pain sensation). To minimize the likelihood of including persons who have strongly preconceived notions about yoga or who wish to participate in this trial only to obtain free yoga classes that they were planning to pay for anyway, we will exclude potential participants who have practiced yoga for any reason within the past 3 months and for back pain within the past 12 months. Reasons for exclusion will be identified from automated data on ICD-9 diagnoses recorded during all visits over the previous year made by health plan members identified with low back pain-compatible ICD-9 diagnoses, telephone pre-eligibility interviews, and in-person visits. Tables 1 and 2 list the inclusion and exclusion criteria, the rationale for each criterion, and the source of information for each criterion.

**Table 1 T1:** Inclusion Criteria

Inclusion Criteria	Rationale	Source*
Continuing member of Group Health Cooperative	Defined population that is easy to identify, recruit and follow-up	A, TI

20 through 64 years of age	Chronic low back pain in children results from different causes than those we are studying; older persons have higher risk of undiagnosed serious conditions causing low back pain	A

At least one primary care visit for back pain within the past 3-15 months	Efficient method for identifying people who may have chronic low back pain and who have been evaluated by a physician for their problem	A

Non-specific, uncomplicated low back pain, i.e., these ICD-9 codes: 724.2 Lumbago 724.5 Backache, unspecified 724.8 Other symptoms referable to back 846.0-9 Sprains and strains, sacroiliac 847.2 Sprains and strains, lumbar 847.3 Sprains and strains, sacral 847.9 Sprains and strains, unspecified site of the back	These codes are consistent with low back pain that is uncomplicated and specific in nature	A

Physician willing to have patients included in the study	Research policy	**

Lives within 45 minutes travel time from class location	Maximize attendance at classes	A

*A = Automated visit data

*TI = Telephone interview

** = determined by letter to physician before the sample identification

**Table 2 T2:** Exclusion Criteria

Exclusion Criteria	Rationale	Source*
Low back pain has lasted < 3 months	Low back pain not chronic	TI

Bothersomeness of pain score of < 3	Back pain too mild to be able to detect improvement	TI

Abdominal Aneurism	Back pain due to, or possibly result of, specific	A
Cancer, metastatic	disease/condition	A, TI
Discitis		A
Disk disease		A
Fracture of vertebra		A, TI
Infectious cause of back pain		TI
Pregnancy		TI
Scoliosis, severe or progressive		A, TI
Spinal stenosis		A, TI
Spondylolisthesis		A, TI

Sciatica	Back problem of complicated nature, including medico-legal issues	TI
Seeking/receiving compensation/litigation for back pain		TI
Surgery, previous back, ever		TI

Blindness	Condition might make it difficult to attend the classes or practice at home	A
Deafness		A
Major Depression		IPE
No CD player for using home practice CDs		TI
Paralysis		A
Psychoses, major		A, TI
Schedules do not permit participation in classes or home practice (including planning to move out of town)		TI
Severe pain when bending or twisting spine		TI
Unable to walk two city blocks		TI
Unable to get up and down from floor		TI
Vision problems, severe		TI
Hearing problems, severe		TI
Lack of transportation		TI

Fibromyalgia, severe	Condition/circumstance might confound treatment	TI
Rheumatoid arthritis/Anklyosing spondylitis	effects or interpretation of data	A, TI
Other disabling chronic conditions (e.g., disabling heart or lung disease, diabetic neuropathy, receiving treatment for hepatitis)		TI
Planning on seeing a health care provider other than primary care provider for low back pain		TI

Dementia	Condition would make it difficult for fully informed consent	A
Unable to read or speak English		TI

Currently using exercise classes or yoga for back pain or has used one in past year; practiced yoga for any reason within past 3 months	Possible bias due to current or recent intervention users	TI

*A = Automated visit data

*IPE = In person examination

*TI = Telephone interview

Members determined to have any of the following during the telephone or in-person screening interviews will be excluded: non-specific causes or potential causes of low back pain (i.e., sciatica, underlying systemic or visceral disease, pregnancy, spondylolisthesis, spinal stenosis, cancer or unexplained weight loss, recent vertebral fracture); current use of yoga for their back pain or a back-specific exercise class or use in the past year; contraindication for yoga or exercise (e.g., severe disk disease); characteristics complicating the interpretation of findings (i.e., involved with litigation or compensation claim for back pain, evidence of severe or progressive neurologic deficits, previous back surgery, planning to seek other treatment for back pain, unstable medical or severe psychiatric conditions, major depression as determined by a score of 10 or greater on the Patient Health Questionnaire (PHQ)-8 [23]; inability to complete the study protocol (i.e., unable to speak or read English, plan to move out of town).

Recruitment procedures

Because the study intervention involves classes, we will recruit participants in seven cohorts consisting of 30 individuals each. We plan to recruit Group Health members who have made visits to their primary care physician for low back pain and whose pain has persisted for at least three months. However, if necessary to meet our recruitment goals, we will also post flyers in the Group Health primary care clinics and advertise in Group Health's quarterly magazine. Finally, in regions with fewer Group Health members, we may advertise the study to the general population.

Automated visit data will be used to identify Group Health members who have made visits to a primary care physician resulting in a diagnosis of low back pain. Those with diagnosis codes during the prior year corresponding to the exclusion criteria (e.g., paralysis) will be excluded. Primary care physicians will be given an opportunity to exclude *all *of their patients from receiving an invitation to participate in the study. Three months after their visit, potential participants will be mailed an invitation letter that explains the study and principal eligibility requirements, and invites participation. We will also include a reply card and a self-addressed, postage-paid envelope on which persons interested in the study can write their names and contact information and mail back to our study staff. An interviewer will then phone the members who respond to answer questions and determine provisional eligibility using a computer program that guides the interviewers through a series of screening questions. The screening process ends with documentation in a database of either ineligibility or provisional eligibility.

If provisionally eligible, the member will be invited to the clinic to confirm eligibility and obtain informed consent. After obtaining consent for the in-person examination, a trained study nurse will examine the patient to rule out sciatica, severe psychiatric conditions (i.e., a physician diagnosis of schizophrenia or bipolar disorder) and major depression (i.e., PHQ-8 score of more than 10) [23]. If confirmed eligible, a research specialist will guide the prospective participant through the consent form, including the elements required by the US Health Insurance Portability and Accountability Act. The study nurse will then obtain baseline physical measurements (Physical Impairment Inventory). After the physical examination, the participant will be taken to a nearby room where an interviewer will administer the baseline questionnaire using a computer assisted interviewing program.

### Randomization to treatment groups

After completing the baseline assessment, participants in each cohort will be randomized, in a 2:2:1 ratio, to the yoga, therapeutic exercise or self care groups. Treatment group will be automatically assigned by a computer-generated sequence of random numbers using a program that ensures that treatment allocation cannot be changed after randomization. Participants will be randomized in blocks of varying size to ensure balanced but unpredictable assignment of participants to all groups. The sequence of randomization and blocking factor will differ for each cohort. All participants will be given the saliva collection kits and instructions for collecting the baseline saliva samples. Participants randomized to the yoga or exercise classes will be given a sheet of paper with their class time, study contact information and a map showing their class location. Just prior to the first class, participants randomized to yoga or exercise will be given a reminder call of their class time. Participants randomized to the self care group will receive a book about self-management of back pain (The Back Pain Helpbook[24]).

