### Statistical issues

#### A. Sample size and the detectable difference

Because patient function (or dysfunction) is generally considered the more consequential of our two primary outcome measures [27] (the other being bothersomeness of back pain), sample size calculations are based on the Roland-Morris Disability Questionnaire (RDQ). Our sample size is designed to ensure that we have good power to detect a clinically significant difference of 2.5 points for pairwise comparisons (yoga to self care and yoga to exercise) on the RDQ (Aim 1 and 2) and adequate power to detect a difference of 1.7 points between the yoga and exercise groups that would be of interest when exploring mechanisms of action (Aim 3). We think that a smaller detectable difference between yoga and exercise can be justified when examining mechanisms of action because in the Aim 3 comparison of yoga and exercise, we focus on the *additional *benefits of yoga compared with exercise, anticipating that a portion of yoga's clinical effects would actually result from movement.

We have accommodated these dual power needs by proposing a 2:2:1 randomization ratio (yoga: exercise: self care), with a total of 210 participants. Assuming 10% loss to follow-up (which is slightly higher than in our previous study [19]), there would be outcomes data for 75:75:38 participants in the yoga, exercise, and self care groups, respectively. To protect against multiple comparisons, we will use Fisher's protected least significant difference approach, which has been shown to have desirable properties when there are three groups [51]. This approach makes pair-wise comparisons between the three treatment groups only if the overall *F*-test is significant. The power of this omnibus *F*-test depends on how the means from the three treatment groups differ. We therefore assumed that the yoga group would be 1.7 RDQ points superior to the exercise group, which would, in turn, be 0.8 RDQ points better than the self care group (giving a difference of 2.5 points between the yoga and self care groups). We chose a 1.7-point difference between yoga and exercise because it is slightly more conservative (i.e., smaller) than that found in our previous study [19].

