#### B. Statistical analysis

We will analyze outcomes from all follow-up time points in a single model, adjusting for possible correlation within individuals using generalized estimating equations (GEE) [55]. Because we cannot reasonably make an assumption of constant or linear group differences over time, we will include an interaction between treatment group and time point. In this case, the multivariate model that includes all time points provides very similar results to fitting separate analysis of covariance models over time and should not substantially influence statistical power.

We also plan to adjust for other baseline characteristics. Specifically, gender, age, pain traveling below the knee but not meeting the criteria for sciatica, job related activity, and Body Mass Index. In a randomized trial of this size, most baseline values and other covariates are unlikely to differ between randomized groups. However, inclusion of baseline covariates can improve the precision of the estimate and therefore increase power to detect differences.

We will use an intent-to-treat approach in all analyses, *i.e*., individuals will be analyzed by randomized group regardless of participation in any classes. This minimizes biases that often occur when participants not receiving assigned treatments are excluded from the analyses. The linear regression model (analysis of covariance) we will use is of the form:

where *Y*(*t*) is the response at follow-up time *t*, *Baseline *is the pre-randomization value of the outcome measure, *Trt *includes dummy variables for the yoga and exercise groups, *Time *is a series of dummy variables indicating the follow-up times, and *z *is a vector of covariates representing other variables being adjusted for. (Note that α_1_, α_2_, α_3_, and α_4 _are vectors.) The referent group in this model is the self care group at the first follow-up time. The models will be fitted using GEE to take into account possible correlation within individuals over time. For each follow-up time point that the omnibus *F*-test is statistically significant, we will go on to test whether there is a difference between yoga and self care to address Aim 1 and a difference between yoga and exercise to address Aim 2.

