Based on similar studies on this study population we expect to have at least a 90% follow-up rate which reduces the potential for bias due to loss of follow-up. Therefore, our primary analysis will be a complete case analysis including all observed follow-up outcomes, but we will adjust for all baseline covariates that are predictive of outcome, probability of being missing, or differences between treatment groups. We will also conduct sensitivity analyses using an imputation method for non-ignorable non-response to evaluate if our results are robust in the complete case analysis [56]. We will report both results in our manuscript.

To help us further understand the benefits of yoga as a treatment for back pain, we will explore possible interactions between treatment groups and covariates. For example, we will consider interactions of the treatment group and the baseline value that would indicate the effect of treatment depends on status at baseline. We will also test for significant interactions of treatment group with other variables (*e.g*., gender) to determine if treatment differences are modified by these variables. We will use similar methods to analyze secondary outcomes including disability days and satisfaction with care.

If we find that yoga is more effective than self care or exercise we will move to Aim 3 with the goal of exploring whether the beneficial effects of yoga on our primary outcomes are mediated through certain measured variables. As mentioned in Figure 1 and Table 4, we are interested in four major classes of measures that could mediate the effects of yoga on back pain outcomes: (1) physical function, (2) cognitive appraisal, (3) affect and stress, and (4) neuroendocrine function. In the interest of parsimony, we will narrow down the number of perspective variables within the four major classes of proposed mediators by using a modification of the framework described by Baron and Kenney [57].

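### Randomisation is blocked within seven cohorts, but cohort is not among the covariates named for the primary model; the likely cost is a slightly overstated standard error and up to about 2 points of power

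*Protocol article*

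**What the plan says.** In the protocol article, the recruitment procedures (under Inclusion and exclusion criteria) state that "we will recruit participants in seven cohorts consisting of 30 individuals each". Randomization to treatment groups adds that "participants in each cohort will be randomized, in a 2:2:1 ratio, to the yoga, therapeutic exercise or self care groups", in blocks of varying size, and that "The sequence of randomization and blocking factor will differ for each cohort".

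Statistical issues, B. Statistical analysis, gives the primary model: baseline value of the outcome, treatment, time, treatment by time, and a vector z of other covariates. These are listed by name: "Specifically, gender, age, pain traveling below the knee but not meeting the criteria for sciatica, job related activity, and Body Mass Index". On correlation it says: "The models will be fitted using GEE to take into account possible correlation within individuals over time". For the complete-case primary analysis it adds that "we will adjust for all baseline covariates that are predictive of outcome, probability of being missing, or differences between treatment groups". Cohort is not mentioned anywhere in Statistical issues.

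**The concern.** A separate blocked list per cohort makes cohort a stratification factor, with about 12:12:6 participants per cohort. Cohorts are enrolled as successive class series. The recruitment text also allows flyers, magazine notices and, in some regions, general-population advertising if they are needed, so cohorts could differ in outcome.

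Blocking removes between-cohort variation from the treatment comparison. A model without cohort does not know this and leaves that variation in the residual. The reported standard error then exceeds the true one, and some of the power gained by the design is not used. The contrast with least slack is yoga against exercise at 1.7 RDQ points, where the stated power is 80%.

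**Working it through.** **Inputs from the protocol** (A. Sample size and the detectable difference): "2:2:1 randomization ratio (yoga: exercise: self care), with a total of 210 participants"; "Assuming 10% loss to follow-up"; 75:75:38 evaluable; RDQ SD adjusted for baseline 3.68; differences of 1.7 (yoga-exercise) and 2.5 (yoga-self care); alpha 0.05, taken as two-sided.

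**Assumed input:** v, the share of residual variance lying between cohorts. No figure is given. I use 2%, 5% and 10%, with 0 and 20% as outer cases, and treat 3.68 as including it.

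**Step 1, the plan's own power.** Pairwise power = Φ(difference/SE − 1.96).
- Yoga-exercise: SE = 3.68 × √(1/75 + 1/75) = 0.601. At 1.7: Φ(2.829 − 1.96) = 80.8% (stated 80%). At 2.5: 98.6% (stated 98%).
- Yoga-self care: SE = 3.68 × √(1/75 + 1/38) = 0.733. At 2.5: Φ(3.412 − 1.96) = 92.7% (stated 92%).
- Omnibus F with 2 and 185 df: 92.6% (stated 92%).

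All reproduce without cohort in the model.

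**Step 2, overstatement of the SE.** With cohort fitted, the residual SD is multiplied by √(1 − v), so the SE without cohort is too large by 1/√(1 − v) − 1. For v = 0.10: 1/√0.90 − 1 = 5.4%.

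**Step 3, effect on the test.** Simulation: seven cohorts of 30, allocation 12:12:6, 10% random loss, one time point, robust SE, 4,000 runs per setting, no class effect.

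| v | SE overstated (formula) | Omnibus rejection with no true effect, without / with cohort | Power at 1.7, without / with cohort |
|---|---|---|---|
| 0 | 0% | 5.0% / 5.0% | 79.8% / 80.0% |
| 0.02 | 1.0% | 5.2% / 5.5% | 80.8% / 81.2% |
| 0.05 | 2.6% | 5.1% / 5.6% | 82.3% / 83.3% |
| 0.10 | 5.4% | 4.4% / 5.7% | 83.1% / 85.2% |
| 0.20 | 11.8% | 3.3% / 5.4% | 83.0% / 88.5% |

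The Monte Carlo standard error of a 5% rate is √(0.05 × 0.95/4000) = 0.3 points.

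At v = 0.10 with no true effect, the true sampling error of the yoga-exercise estimate is 0.571 without cohort and 0.568 with it. The mean reported SE is 0.595 and 0.569. So the estimate is about equally precise either way, and only the model without cohort misreports it. The simulated overstatement, 0.595/0.569 − 1 = 4.6%, is a little below the formula because the realised variance among only seven cohorts averages 6/7 of the nominal value: √((0.90 + 0.10 × 6/7)/0.90) − 1 = 4.7%.

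**Step 4, clustering within classes.** Assume one class per arm per cohort, a class ICC of 0.05 in the two class arms, and v = 0.05. With no true effect, the true sampling error for yoga-exercise is 0.717 without cohort and 0.716 with it. The reported SE is 0.594 and 0.576. Omnibus rejection is 9.2% and 10.6%. At 0.02 for both, rejection is 6.7% and 7.1%. Reported SEs are now too small, and cohort indicators alone lower them further.

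**Step 5, cost in degrees of freedom.** 75 + 75 + 38 = 188 observations at one time point, less an intercept, two treatment terms, baseline and at least five covariates, leaves about 180. Six cohort indicators use six of these.

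**The case against.** The best defence is that the plan already covers this. Cohort is fixed before randomisation, harm arises only if it predicts outcome, and predicting outcome is one trigger for adding a covariate to the primary analysis. This stands in part. The clause does not name cohort and leaves its entry to a screen of the data. The imbalance trigger is unlikely to fire, because blocking balances cohort across arms. A randomisation stratum should be in the model by design.

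A second defence is that this is a condensed article whose SAP is not shown. That lowers the weight of the point but does not remove it, because the article fixes the covariates by name.

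The objections on size stand in full. No between-cohort variance is given, varied recruitment routes are only a possibility, and at 2% or less the two models do not differ materially.

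A reader might infer that the treatment estimate itself is less precise, or that power falls short of plan. Neither is supported: true sampling error is nearly unchanged, and the stated power was computed with baseline adjustment only and reproduces. A reader might also infer that the trial's standard errors are too large overall. That is unsafe: two arms are taught in groups, the model allows only for correlation within individuals, and class clustering acts in the opposite direction.

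**Conclusion.** The omission is clear from the document; its effect is small and conditional. If cohorts differ after baseline adjustment by an assumed 2% to 10% of residual variance, the reported SE is overstated from this source by about 1.0% to 5.4%, and about 0 to 2 points of power are forgone for the 1.7-point yoga-exercise contrast. At 20% the loss would be about 5 points (88.5 − 83.0 = 5.5). The omission causes no bias, no excess of false positives and no shortfall against the stated power. Conservatism becomes visible in the simulated error rates only from about 10%. These sizes assume no class effect; the net direction of error in the trial's standard errors also depends on class clustering, for which the protocol gives no figure.

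**What to change.** Name cohort as a fixed effect (six indicators in z) in the primary model for both primary outcomes, and in the models for secondary outcomes, regardless of whether it proves predictive. In the same text, state how clustering within yoga and exercise classes is handled, for example by a random class effect in those two arms only, with a method suited to few classes. Cohort should not be added without this second part.

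The cohort terms cost six of about 180 residual degrees of freedom and one line of specification. No new data are needed: cohort is known from the randomisation, and class attendance is already recorded. The class allowance may widen the intervals, but that reflects the design and is not a cost of adding cohort.
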